### Eligibility

All general practices in the Region of Southern Denmark will be eligible to participate in the study.

All clinic staff conducting patient consultations are eligible for inclusion, this including doctors, nurses, and other HCPs. Not all staff have to be enrolled in the study for the practice to be included. Each practice is allowed to decide whether all staff or only a selected group of staff will be participating in the study. All patients ≥ 18 years old affiliated with the participating practices are eligible.

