**Fig. 2 Fig2:**
[figure not shown]
Timeline of the Identification and Treatment of Alcohol Problems in Primary Care (iTAPP) Study. Stepped wedge cluster randomized controlled trial design with general practices in The Region of Southern Denmark

HCPs will register consultations in which alcohol is addressed from the start of the baseline period and throughout the study period (described below). Patient questionnaires will be sent four times during the study period; once during baseline, twice during implementation, and once at the end of the follow-up period.

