### Data collection

#### Frequency of alcohol related consultations in the practices

The HCPs will register any consultation in which the topic of alcohol is raised using the International Classification of Disease tenth revision (ICD-10) code Z00.6 (Encounter for examination for normal comparison and control in clinical research program) [60] as secondary diagnosis to the consultations main diagnosis. In the case of no primary diagnosis to the consultation, the HCPs will use the International Classification of Primary Care 2 (ICPC-2) code A97 (no disease) [61, 62] together with the ICD-10 Z00.6 code. The HCPs will use the codes from start of baseline and throughout the study period. Any consultation in which alcohol consumption and/or alcohol-related problems is addressed will count as an observation regardless of whether the 15-method has been used.

Further, data on smoking, exercise, alcohol, and weight will be collected along with the total number of face-to-face consultations (including video consultations) in the practices from baseline to end of study. Local registration codes are available, among others, on smoking status (daily, occasionally, quit, never), exercise (hours per week), alcohol intake (standard units per week), and weight in all Danish general practices [63, 64].

Data will be collected on practice level only. A data quality assessment will be conducted during step two (Fig. 1) in a sub-sample of practices.

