### Procedures

#### Power and sample size calculation

We hypothesize that the implementation of the 15-method can lead to a 10% reduction in the proportion of patients exceeding the Danish low-risk alcohol consumption limits of ten standard units per week and a maximum of 4 standard units per drinking day for women and men, in the practices participating in the study. In the Region of Southern Denmark, the proportion of adults exceeding the national alcohol consumption limits is 14.2% [81]. We further hypothesize that the implementation of the 15-method will increase the proportion of consultations in which the topic of alcohol is addressed from 5.3 to 9.8% [82] in the participating practices.

Calculations follow power and sample size calculations in stepped wedge cluster randomized trials [83, 84], resulting in a total of 16 general practices being randomized to the 15-method in four steps of four practices (clusters). A power calculation was conducted for each of the two objectives, i.e., lowering the proportion of patients exceeding the low-risk alcohol consumption limit, and increasing the likelihood of alcohol use being addressed during a consultation. Sample size estimates were based on the most conservative result of the two. We expected an average of 1538 patients per GP in the region [85], 2.3 GPs per practice [85], 89% of patients within the targeted age-group (≥ 18 years) per general practice [86], and an estimated response rate in the patient questionnaires of 50% [87–89]. To detect the difference between the proportions 14.2% and 12.8% (10% reduction) using an exact binomial test of proportions with a 2.5% significance level and with an expected intraclass correlation coefficient of 0.068 [90], an estimated power of > 90% was obtained.

With a total of 16 general practices, a power of 81% can be achieved with a patient questionnaire response rate of 37%.

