### Analysis plan

#### Quantitative analyses

Analyses will be conducted by intention-to-treat principle [92]. Binary outcomes will be analyzed using mixed model logistic regression. Continuous outcomes, e.g., number of heavy drinking days, the use of biomarkers, and pharmacological prescription frequency will be analyzed using mixed model linear regression. Outcomes will be analyzed on practice level with weighted observations according to patient population size and number of participating HCPs in the practice [93].

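### The weights named for all outcomes (list size and number of participating staff) do not match the respondents and consultations that carry the information in outcomes 1 to 3

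*Protocol article*

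**What the plan says.** The protocol article, under Quantitative analyses, gives one weighting rule for every outcome: "Outcomes will be analyzed on practice level with weighted observations according to patient population size and number of participating HCPs in the practice". The same paragraph says "Binary outcomes will be analyzed using mixed model logistic regression", assigns linear mixed models to continuous outcomes, and states "Analyses will be conducted by intention-to-treat principle".

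Other sections describe where the data come from:

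- **Outcomes 1 and 3** (share above the low-risk limit; heavy drinking days) come only from patients who answer the questionnaire, sent four times: "once during baseline, twice during implementation, and once at the end of the follow-up period".
- **Outcome 2** (alcohol addressed in a consultation) comes from registration codes. They are collected "along with the total number of face-to-face consultations (including video consultations) in the practices from baseline to end of study".
- **Outcomes 4 and 5** (biomarkers, prescriptions) come from national registries at practice level.
- **Staff participation** is left to the practice (Eligibility): "Each practice is allowed to decide whether all staff or only a selected group of staff will be participating in the study".

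The power section assumes 50% response and gives power above 90%, falling to 81% at 37% response. Trial status spring 2024 reports an average response of 30%.

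**The concern.** A weight should reflect how much an observation tells us, or which population the estimate is meant to describe. For a practice's survey proportion, the information is set by how many people answered. For the consultation outcome it is set by how many consultations took place. List size is neither. The power section accepts this, because its result depends on response. A list-size weight is the same whether 10% or 50% of a practice replies.

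The staff count raises a different problem. It is chosen by the practice, so it partly measures engagement and partly practice size. It is not a measure of precision for a survey outcome. If the effect is larger where more staff take part, weighting by the count favours the practices where the method was taken up most, while the stated purpose is to judge suitability for national roll-out.

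Both main aims are affected. At stake are the width of the confidence intervals, possibly the false-positive rate, and the meaning of the estimated effect.

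**Working it through.** **Inputs from the protocol article.** 1,538 patients per GP, 2.3 GPs per practice, 89% adults, 16 practices, 14.2% against 12.8%, significance level 2.5% (sidedness not stated), ICC 0.068, response 50% and 37% (power section) and 30% (trial status).

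**Step 1: counts per practice.** Adults listed: 1,538 × 2.3 × 0.89 = 3,148. Respondents: × 0.50 = 1,574; × 0.37 = 1,165; × 0.30 = 944.

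**Step 2: reproduce the stated power from respondents.** Two calculations at one-sided 2.5%:

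- Simple comparison of two proportions, n per arm = 16 × respondents / 2 (12,593 at 50%; 9,319 at 37%), no ICC. SE = √[(0.142 × 0.858 + 0.128 × 0.872) / n] = 0.00431 and 0.00501. Power = Φ(0.014 / SE − 1.96) = 0.902 and 0.799. With exactly 10% reduction (12.78%) it is 0.910 and 0.810.
- Hussey-Hughes stepped-wedge variance, ICC 0.068, four surveys, fresh respondents at each, and 4 then 12 practices exposed at the two middle surveys (assumed placement): 0.921 and 0.826.

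Both agree with the stated figures (above 90% and 81%) to within two points. With a two-sided 2.5% test they give 0.844/0.711 and 0.870/0.745, which do not agree. So respondent counts lead back to the protocol's own figures. At 30% response the same one-sided calculations give 0.71 and 0.74.

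**Step 3: list size used as the binomial denominator.** Sampling variance is proportional to 1/n. Replacing respondents by list size multiplies the SE by √(response rate). The true type I error is then 1 − Φ(1.960 × ratio) for a one-sided 2.5% test and 2 × [1 − Φ(2.241 × ratio)] for a two-sided one.

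| Response | Respondents per practice | SE ratio | One-sided 2.5% | Two-sided 2.5% |
|---|---|---|---|---|
| 50% | 1,574 | 0.71 | 8% | 11% |
| 37% | 1,165 | 0.61 | 12% | 17% |
| 30% | 944 | 0.55 | 14% | 22% |

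The ratio carries over to the stepped-wedge model of step 2: SE 0.00294 with all 3,148 adults against 0.00536 with 944 respondents, a ratio of 0.55. An illustrative simulation (16 practices, four surveys, 30% response, true effect −0.014, assumed spread of practice sizes) gave a model SE of 0.0031 against a true SD of 0.0056, and 73% coverage of the 95% interval. Respondent denominators gave 0.0057 against 0.0055, and 95% coverage.

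**Step 4: list size used only as a relative weight, residual variance estimated.** With list size l and respondents n per practice, the sampling variance relative to respondent weighting is [Σ(l²/n) / (Σl)²] × Σn. Averaged over simulated sets of 16 practices with assumed sizes, it is 1.01 if response varies over 25–35%, 1.04 over 20–40%, and 1.19 over 10–50% (all assumed ranges).

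**Step 5: the staff-count weight.** In the simulation of step 3:

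- With a constant effect, every weight was unbiased (means −0.0139 to −0.0140). Weights involving the staff count had SD 0.0058 to 0.0061 against 0.0055, so variance rises by (0.0058/0.0055)² − 1 = 11% to (0.0061/0.0055)² − 1 = 23%.
- With an effect that grows with the share of staff taking part (assumed gradient), the estimate moved from −0.0140 to −0.0151, that is 0.0011/0.0140 = 8%.

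**The case against.** The strongest reply is that the sentence speaks of weighted observations and names no denominator. How weights enter a model is detail that an article commonly leaves to the SAP. This stands as far as it goes, and it rules out one tempting reading: that the plan does misstate precision by the factor in step 3. That follows only if list size is the denominator. A logistic model of practice-level proportions does need a count, and list size is the only patient count the section names, but the text does not settle the matter. What the reply does not answer is that the rule is stated, covers outcomes 1 to 3, and names quantities other than those that determine their precision.

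A reader might also infer that the staff weight breaks intention-to-treat. The documents do not support that. A weight fixed before allocation leaves every practice analysed by its randomized launch date and only changes which average is estimated. The principle is threatened only if the count can change after allocation. Practices learn their allocation during baseline and are trained shortly before launch, so a change is possible, but nothing says that the count is updated.

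A large distortion from the staff weight is likewise unsupported. If the effect were strictly proportional to the number of participating staff with an assumed coefficient of variation of 0.5, the weighted effect would be 1 + 0.5² = 1.25 times the average practice effect. Neither assumption comes from the documents, and the staff count also reflects practice size.

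Two further points stand. For registry outcomes 4 and 5, patient population size is a sensible denominator. For outcome 2, the staff count may reflect how much of a practice's activity gets coded. That is a question of recording coverage, which a weight does not repair and which total consultations as the denominator does not fully resolve either.

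**Conclusion.** The point holds for outcomes 1 to 3. The named weights are not the quantities that carry the information, and they sit badly with a power calculation driven by response.

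The size depends on a use that the article leaves open. As a denominator at 30% response, list size gives standard errors of about 0.55 of their correct size and a type I error of about 14% (one-sided) or 22% (two-sided) for a nominal 2.5% test. As a relative weight with estimated residual variance, it costs about 1 to 19% in variance under assumed response spreads and does not by itself inflate false positives.

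The staff-count weight has no precision rationale for the survey outcomes. It loses some precision and shifts the target towards more engaged or larger practices, by about 8% in one simulation with an assumed gradient. It changes the estimand. Intention-to-treat is at risk only if the count can change after allocation. The criticism of list size does not extend to outcomes 4 and 5.

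**What to change.** Replace the single weighting rule with a denominator for each outcome:

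- **Outcomes 1 and 3:** model individual responses with practice random effects. For the binary outcome 1, respondents exceeding the limit out of respondents, per practice and survey, as a binomial is an alternative.
- **Outcome 2:** model coded consultations out of total consultations as a binomial, with practice random effects. State whether consultations by non-participating staff are in the total.
- **Outcomes 4 and 5:** keep adult list size (list-time) as the denominator.
- **Staff participation:** drop it as a weight in the main analyses. Use it only in a sensitivity or exploratory analysis, with the count as it stood before randomization.

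The cost is a change of wording, to be made before the outcome data are analysed, and possibly wider confidence intervals than the weighted analysis would have shown. No new data are needed: the survey yields the respondent counts, consultation totals are already collected, and list size is already needed for the planned weights.

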#### Qualitative analyses

The CFIR interview guide [56] will constitute the basis of the coding framework. The CFIR guide (cfirguide.org) supplies a pre-populated coding template that will be utilized for coding. The deductive approach [94] of using the preset coding tree from the CFIR template will be complimented by abductive analysis [95, 96] to allow for unexpected findings and theoretical considerations to the identified determinants. The CFIR framework can describe contextual factors and help generate hypotheses for implementation success or failure, but it does not adhere to a single theory to explain actions behind the effects of the determinants [56, 97]. By allowing for potential new insights via an abductive approach, considerations to the theoretical underpinnings behind the identified determinants becomes possible. Interviews will be transcribed verbatim by [name] and a research assistant and [name] will conduct the initial coding. Double coding will be conducted on a sub-set of data for reliability measures and discrepancies or disagreements will be discussed within the research team. Practices will be created as cases based on their characteristics and CFIR constructs will be rated across cases. Cases will then be analyzed across CFIR constructs using Nvivo framework matrices and case classification supplied by hierarchy charts. The research team will discuss data saturation [98] and information power [99] to ensure adequate levels of collected data.

The Framework for Reporting Adaptations and Modifications to Evidence-Based Interventions (FRAME) [58] will be utilized to facilitate a better understanding of local adaptations to the 15-method and differences in the implementation processes in the practices. The FRAME focuses on describing (1) when modifications were made, (2) whether the modification was plan or unplanned, (3) who participated in the decisions about modification, (4) what was modified, (5) level of delivery of the modified intervention, (6) modifications in relation to intervention fidelity, and (7) the rationale for the modification(s) [58]. The analysis of FRAME components will be informed by the CFIR cross-case analyses described above.

Analyses will be conducted using Nvivo 12 [100] or newer.

### Trial status spring 2024

As of March 2024, the iTAPP study includes eighteen practices. The first three clusters are active and use the 15-method in their everyday practice. The process evaluation is underway and currently concluding its data collection phase. Three of the four patient questionnaires have been distributed and yielded an average response rate of 30%. Three practices from the Danish feasibility study of the 15-method in primary care have continued as participants in the iTAPP study. As these three practices were familiar with the 15-method prior to the iTAPP study they are not included among the eighteen practices and data analyses will be kept separate.

## Discussion

The iTAPP study is pragmatic in its approach [101] and the implementation strategy focuses on a flexible engagement of practice staff and managers (GPs). This is done by offering the same training and support to all levels of healthcare professionals (nurses, GPs, assistants) while encouraging them to use the method as they see it best in their practice. The reason for this strategy is three-fold. First, many GPs decline to participate in projects due to time constraints [102]. We address this initial barrier by making the participation as flexible as possible. Second, results from the feasibility study of the 15-method in Denmark indicated that the GPs wanted different levels of involvement with the 15-method intervention and wanted the opportunity to delegate tasks to their staff [32]. Third, results from the feasibility study also indicated that the 15-method was well suited for interdisciplinary collaboration, which improved the feasibility and use of the method.

This study offers a multifaceted perspective, with four key viewpoints. From the patient’s perspective, the 15-method can potentially help identify alcohol related problems at an earlier stage, and provide a flexible treatment offer in a familiar setting. For healthcare professionals, the 15-method addresses a traditionally challenging topic [11, 14] by equipping them with concrete tools, communication training, and clear treatment directives. From a societal perspective, the accessibility of primary care positions GPs uniquely to identify hazardous and harmful alcohol use across diverse age groups, with potential public health and economic benefits through early identification and intervention. Should the iTAPP study substantiate the effectiveness of 15-method in reducing alcohol consumption within a primary care setting, it can form the basis for national roll-out strategies. Finally, it may prompt deliberations regarding the responsibilities and economic incentivization of Danish general practitioners concerning the management of alcohol related problems.

### Methodological considerations

The level of alcohol related consultations is measured in the same way throughout the study. The HCPs are asked to register any consultation in which alcohol is addressed from start of baseline. The knowledge of being observed in this way can potentially introduce a Hawthorne effect prior to intervention implementation. Although the actual impact of the Hawthorne effect is debated [103] the increased focus on registering consultations can potentially decrease the detectable difference to post implementation levels. Given the sample size we do however expect these potential differences to even out.

The 15-method training will be conducted in three-hour sessions, shorter than the original Swedish training. Results from the Danish feasibility study suggested that the Swedish material was too extensive for Danish general practice and that training could be condensed via shortening of the material. Moreover, most aspects of the 15-method are already familiar to HCPs, as they are accustomed to concepts such as MI, patient homework assignments, and opportunistic symptom-based screening. Therefore, the training will serve as a review of familiar concepts while providing a comprehensive introduction to the 15-method to integrate knowledge effectively.

The patient questionnaires will be distributed with consideration to known seasonal variations in alcohol consumption, e.g., holiday seasons. People with low IT-literacy, e.g., elderly and cognitive impaired can opt-out of the electronic mail system through which the questionnaire is distributed. As a results of this, a small patient sample will not be available for collection of questionnaire data. Further, as the questionnaire is distributed four times during the study period, we anticipate some patients will choose not to answer the subsequent questionnaires.

The randomization procedure is conducted on practice level. Randomization on patient level is not possible as the study investigates the effectiveness of the intervention on the initial screening procedure among non-selected patients. Further, a randomization by HCPs would increase the risk of spillover effect within the practice.

The study’s stepped wedge design is a strength as it allows for a brief pilot phase, for continuous evaluations of resources throughout the study, and for logistical considerations regarding implementation and support. The design follows the MRC framework for complex interventions and builds on feasibility testing [32] and pre-trial adjustments to the intervention. Another strength is the imbedded process evaluation which can help describe relationships between context, mechanisms of impact, and study outcomes.

**Table 1 Tab1:** Objectives, hypotheses, outcome measures, data sources and data collection timepoints in the Identification and Treatment of Alcohol Problems in Primary Care (iTAPP) Study. Stepped wedge cluster randomized controlled trial design with general practices in The Region of Southern Denmark

Objective	Hypothesis after implementation of the 15-method:	Outcome measure	Data source	Data collection timepoint
i) To evaluate the 15-method’s effectiveness in lowering the proportion of patients who exceed the Danish low-risk alcohol consumption levels.	The proportion of patients exceeding the Danish national low-risk alcohol consumption limits will be reduced.	Proportion of patients exceeding the Danish low-risk alcohol consumption limit of ten standard units per week and a maximum of four standard units on a single day for men and women.	Questionnaires to all patients 18 + years affiliated with participating practices including the AUDIT-C, and TLFB one week version.	Four times during trial. Illustrated in Fig. 2.
ii) To evaluate the 15-method’s effectiveness in increasing the likelihood of alcohol use being addressed during a consultation in general practice.	Alcohol related consultations will occur more frequently in the general practices.	The likelihood of alcohol use being addressed during a consultation in general practice.	Registration codes from practice patient filing systems: ICPC-2 code A97, and the ICD-10 code z006.	Once during the trial period (data quality control). Once at end of follow-up period.
iii) To evaluate the 15-method’s effectiveness in lowering the number of heavy drinking days per week in patients.	The number of heavy drinking days will decrease in the patient population.	Number of heavy drinking days (> 4 standard units on one day for men and women) per week in patients.	Questionnaires to all patients 18 + years affiliated with participating practices including the AUDIT-C, and TLFB one week version.	Four times during trial. Illustrated in Fig. 2.
iv) Evaluate the frequency of use of biomarkers as a screening tool for harmful alcohol use.	The use of biomarkers as a screening tool for harmful alcohol use will increase.	The use of the biomarkers ALAT and GGT.	The Danish National Laboratory Database.	End of follow-up period.
v) Evaluate the prescription rate of pharmacological treatment for alcohol problems.	Prescriptions of pharmacological treatment for alcohol problems will increase, as the HCPs become more aware of use cases and more familiar with treatment options through academic detailing.	Prescription rate of Disulfiram, Naltrexone, Acamprosate and Nalmefene.	The Danish National Prescription Registry.	End of follow-up period.

*Notes* One standard unit defined as 12 g of ethanol; AUDIT-C, Alcohol Use Disorder Identification Test Consumption; TLFB, Timeline Follow Back; EQ-5D, European Quality of Life 5 Dimensions; WHO-5, World Health Organization Five Well Being Index; ICPC-2, International Classification of Primary Care 2; ICD-10, International Classification of Disease tenth revision; code A97, no disease; code z006, Encounter for examination for normal comparison and control in clinical research program; ALAT, Alanine Transaminase; GGT, Gamma-Glutamyl Transferase; HCP, health care professional

